#### Qualitative Data Analysis Plan

For qualitative analysis, we will use the user-experience “honeycomb” framework described by Morville [30]. This approach was used to test health education applications, a decision aid tool [33-36], and the systematic review library of the Cochrane Collaboration [37]. For the purposes of our study, we will use the following 5 (of 7) dimensions:

Useful: whether the brochure is useful for decision-making about the screening testValuable: whether the brochure improves participants’ knowledge about CRC and screeningCredible: whether the information in the brochure is perceived as credibleUsable: whether the information is clear and easy to understandDesirable: whether the participants are satisfied by the brochure or whether they have suggestions about how to improve it

The qualitative data will be analyzed using MAXQDA software (VERBI Software GmbH) [38].

## Results

### Overview

As of September 2022, a total of 515 participants had been enrolled in the trial and sent intervention or control materials. Six months later, 98.8% (509/515) of the enrolled individuals were sent the follow-up questionnaire. Data collection was completed on July 24, 2023 (6-8 months after the intervention).

We expect that the proportion of participants who complete the screening test appropriate to their risk level will be higher in the intervention group than in the control group, except for the individuals at moderate risk. The proportion of participants at moderate risk in the intervention group is expected to be the same as that of the participants in the control group in screening test choice because both tests are suggested as equal options.

We do not expect any difference in anxiety between the intervention and control groups. A Cochrane review of interventions similar to ours has shown that there was a nonsignificant trend toward decreased anxiety with risk information (standard mean difference in anxiety 0.13, 95% CI −0.29 to 0.03) [17].

Our intervention does not aim to enhance overall screening uptake; therefore, we do not expect any difference between the groups.

### Dissemination of Results

We plan at least 5 open-access publications based on the trial data. Intermediate and final reports will be sent to the funding institution and to the ethics committee. Participants will be informed about the results of the trial on request. We communicate regularly with the Vaud organized CRC screening program and will encourage it to implement components of this approach if it is found effective.

Suggestions for oral communications and publications as well as names of authors will be discussed during the meetings of the steering committee. The principal investigator should be considered for the role of lead author. Disputes regarding authorship will be settled by the principal investigator and the steering committee.

## Discussion

### Testing the Impact of Risk Communication and Recommendations on Screening Behavior

Although many experts have recommended personalized CRC screening as a means of optimizing the risk-benefit balance for individuals and improving the use of scarce gastroenterology resources, this approach has not been implemented to date in an organized screening program. This study aims to demonstrate the effect of personalized information materials on individuals’ choice of screening test to assess the feasibility of a larger trial evaluating the effect of personalized screening recommendations on clinical outcomes such as advanced neoplasia detection rate and CRC screening uptake. The trial addresses a current need of the Vaud screening program to demonstrate to the public and to physicians that individuals at low risk can be safely directed toward the FIT.

This trial is one of the rare studies that tests the impact of risk communication and recommendations on screening behavior. Although it may seem evident that communicating individuals’ risk level would influence their screening behavior, previous studies have shown increased knowledge but little effect on test choice [17]. This presents a potential limitation in the implementation of personalized screening programs: unless these programs restrict the choice of participants, risk calculation may have no effect.

There are other means of personalizing CRC screening. Several strategies rely simply on participants’ sex or race. In Sweden and Norway, different cutoffs are used to define a positive FIT result requiring colonoscopy [39]. In Germany, colonoscopy screening is recommended at age 50 years for men and age 55 years for women. The American Gastroenterology Society recommends screening at a younger age (45 years) for African Americans. Another approach is to use quantitative FIT results below the positivity threshold but above 0 to define shorter intervals between FITs [40]. We chose to use multiple factors to define baseline risk following recommendations from the BMJ Rapid Recommendations team [12] and because of the strains on colonoscopy capacity in the canton of Vaud [18].

The strengths of this study include its *patient and public involvement in research* approach for the development of study materials; nesting within an organized screening program; population-based sampling to obtain the estimates of participation in the general population; both quantitative and qualitative evaluations, which should permit us to obtain a preliminary estimate of not only efficacy but also acceptability and potential improvements; the use of theory (the Health Belief Model [25]) to inform the intervention and evaluation; and randomization and rigorous design for a pilot study.

Potential weaknesses include the need for informed consent beyond what is typically needed in an organized screening program, which could decrease participation and increase selection bias. As such, we might underestimate eventual participation and overestimate acceptance, assuming that we preferentially include persons motivated to be screened. This selection bias could exclude populations considered more vulnerable, such as individuals with poor health literacy. However, the study materials were written, to the extent legally possible, using plain language. We did not translate the study materials into other languages, but all invitations from the screening program are also in French, with other languages only available on request. The Vaud screening program requested that we not invite individuals already participating in screening at regular intervals with the program because screening recommendations made in the study may differ from those made by the program and thus create confusion. We sought to avoid inviting for this study individuals who had not participated after being sent an invitation to the program, fearing that our participation rate would be too low. As a result, our sample population is heavily weighted toward younger age groups (those aged 50-54 years), and we may have a larger-than-expected proportion of participants at low risk of CRC.

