### Study Design and Setting

We will perform a 2-arm randomized superiority controlled trial with participants randomized 1:1 in 2 arms: intervention and usual care. Participants, but not the investigators, will be blinded. The statistician performing the primary outcome analyses will be blinded to group assignments. The trial will be nested in the Vaud CRC screening program.

We used a *patient and public involvement in research* approach throughout by involving 5 members of the target population (residents of the canton of Vaud, Switzerland, aged between 50 and 69 years) in all aspects of the project. This collaboration allowed us to develop materials for our participants that were acceptable, easily understood, and pretested before the trial started. These 5 members will participate in the interpretation and dissemination of the results.

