### Procedure

The study will be conducted in the following 3 phases:

T0: recruitment and baseline data collectionT1: intervention and secondary outcome data collectionT2: follow-up at 6 months (primary outcome and secondary outcome data collection)

At T0, an invitation letter, a consent form, and the baseline questionnaire (questionnaire 1) that allows us to verify the eligibility criteria and calculate the CRC risk score will be sent to the potential participants by the Vaud CRC screening program. The ID codes for the participants will be generated using the IDGenerator, a software tool that was specifically developed for epidemiological and clinical trials [21]. The risk score will be calculated for all eligible individuals who return the signed consent form; subsequently, they will be randomized to either the intervention group or the control group. All individuals who do not respond within 1 month after the first mailing will receive a reminder.

At T1, enrolled participants will receive the intervention or a usual care brochure (in accordance with their group allocation), questionnaire 2, and an information sheet that they can provide to their general practitioner and pharmacist regarding their participation in the study. The participants who do not respond to questionnaire 2 within 2 weeks will be sent a reminder. Qualitative interviews will be conducted with willing participants at this time.

Six months after the intervention, at T2, participants will be contacted again to measure their screening behavior using questionnaire 3. Their responses will be accepted up to 8 months after the intervention. In case of nonresponse within 2 weeks, they will receive a reminder.

All 3 questionnaires, information materials for the participants, and the consent form will be available in both paper and electronic formats. Participants can choose the format that is more convenient to them. All data will be entered into the REDCap (Research Electronic Data Capture; Vanderbilt University) platform [22,23].

Refer to Table 1 and Figures 1 and 2 for procedure details.

**Table 1 table1:** Schedule of enrollment, intervention, and assessments.

		Study period			
		Enrollment	Allocation	After the allocation	
		T0^a^	0	T1^b^	T2^c^

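### The participation and eligibility rates describe only residents never invited to the programme, not the general population the protocol claims, and the 6-week reading leaves at most two weeks for responses to the reminder

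*Protocol article*

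**What the plan says.** The Objectives section commits the trial to a participation rate and a proportion eligible. Textbox 2 (Outcome Measures) lists participation and eligibility as secondary outcomes, each read 6 weeks after the invitation letter. The abstract and the Discussion tie such results to the feasibility of a larger trial.

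The Discussion names as a strength "population-based sampling to obtain the estimates of participation in the general population". The target population in Study Design and Setting is residents "aged between 50 and 69 years". The inclusion criteria narrow this to people not yet invited to a programme rolled out between 2016 and 2022.

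The Discussion gives two reasons for that frame: "The Vaud screening program requested that we not invite individuals already participating in screening at regular intervals with the program", because study and programme recommendations might conflict; and "We sought to avoid inviting for this study individuals who had not participated after being sent an invitation to the program", with the motive "fearing that our participation rate would be too low". As a consequence, it says, "our sample population is heavily weighted toward younger age groups (those aged 50-54 years"), and low-risk participants may be over-represented.

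On timing, the Procedure section states: "All individuals who do not respond within 1 month after the first mailing will receive a reminder". The same section has the risk score calculated for every eligible person who returns a signed consent form, followed by randomisation, and names no closing date.

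The Sample Size Estimation section plans 4300 invitations, 1400 responses (32.56%) and 880 eligible (62.86% of responders).

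**The concern.** A frame that omits two previously invited groups, one of them because it was expected to respond poorly, cannot by itself estimate participation in the population aged 50 to 69. The limitations paragraph does not repair this. It links the age skew to the risk mix, and links a possible underestimate of participation to the consent step. It never says that the frame limits the participation or eligibility estimates, and the general-population claim stands unqualified in the paragraph before.

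The 6-week reading adds a smaller problem. If responses to the reminder arrive after the reading but still lead to enrolment, the reported rate is not the rate that filled the trial.

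What is at stake is planning. The protocol says the risk distribution in the eligible Vaud population is not known, so the pilot's own figures would naturally feed the number of invitations and the expected number of high-risk participants in a full-scale trial. If that trial also approached previously invited residents, these rates would not carry over.

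**Working it through.** **Planned rates, reproduced.** Response: 1400/4300 = 32.56%. Eligibility: 880/1400 = 62.86%. Both agree with the text.

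**Sampling error at the planned numbers.** Half-width = 1.96 × √(p(1−p)/n). Response: p = 0.3256, n = 4300, giving ±1.4 percentage points. Eligibility: p = 0.6286, n = 1400, giving ±2.5 points. Precision is adequate; the question is which population is being described.

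**Claim against frame.**
- Claimed target: the general population (Discussion, strengths).
- Nominal age range: 50 to 69.
- Actual frame: never-invited residents only (inclusion criteria).
- Omitted: regular programme participants and earlier non-participants (Discussion, weaknesses).
- Age mix: skewed to 50-54, with no percentage given.

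**How far the frame could matter (assumed inputs).** The document gives neither the sizes of the omitted groups nor how they would respond. Suppose first that only earlier non-participants are missing, that they form a share s of the target population, and that a fraction r of them would respond. Overall response = (1−s) × 32.56% + s × r.
- s = 20%, r = 20%: 0.8 × 32.56 + 0.2 × 20 = 30.0%.
- s = 40%, r = 10%: 0.6 × 32.56 + 0.4 × 10 = 23.5%.
- s = 60%, r = 5%: 0.4 × 32.56 + 0.6 × 5 = 16.0%.

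On these inputs the frame overstates response. Regular participants are missing too, and might respond more readily than never-invited residents. If the two omitted groups are taken as equal in size, the frame is unbiased when the regular participants' response equals 2 × 32.56% − r. For r = 5%, 10% and 20% this is 60.1%, 55.1% and 45.1%. Above those values the frame understates response; below them it overstates it. Nothing in the document says which side applies.

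Eligibility is equally open. Many regular participants would fail the exclusion for colonoscopy within 9 years or FIT within 1.5 years, so leaving them out tends to raise the proportion eligible. The document gives no figure for earlier non-participants.

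**The 6-week reading.** Six weeks is 42 days and one month is 28 to 31 days, so 42 − 31 = 11 to 42 − 28 = 14 days remain after the reminder falls due. This is an upper bound, because mailing and delivery take part of it. If a share L of eventual responders reply after 6 weeks (assumed), the reading is 32.56% × (1−L):
- L = 5%: 30.9%.
- L = 10%: 29.3%.
- L = 20%: 26.0%.

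Planning 1400 responses from such a reading would call for 4300/(1−L) invitations: 4526 at L = 5% and 5375 at L = 20%, against 4300.

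**The case against.** The strongest reply is that the authors disclose the frame themselves. The inclusion criterion is open, both omissions and the age skew are stated as weaknesses, and no outcome definition uses the general-population wording. On that view one phrase in a list of strengths is too broad. The disclosure is real, but it is attached to the risk mix and the consent step and never to the feasibility rates, so the claim remains uncorrected where it matters.

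Several further objections stand:
- A reader might infer that the frame inflates participation. The document states a motive about one omitted group, not a net effect. The other omitted group could pull the opposite way, and the only direction given outright for participation is an underestimate, from consent.
- A reader might infer that the frame was chosen solely to avoid low response, or that most participants are aged 50-54. Low response was one of two reasons, and no percentage is given for the age band.
- Textbox 2 speaks of a number of completed questionnaires, which might be read as a rate without a denominator. The Objectives promise a rate and the sample size section supplies the denominator, so this reading fails.
- A fixed reading date is a legitimate choice, and the document says nothing about late responses. It also does not state that late responders are enrolled; it only sets no limit that would exclude them.

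Data collection is reported as complete, so the frame itself can no longer change.

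**Conclusion.** The point holds in limited form. The protocol claims a property, estimation of general-population participation, that its sampling frame does not have. The two rates are valid for never-invited residents with a young age mix. For the 50-69 population as a whole, neither the size nor the direction of the bias can be derived from the document; the figures from 16.0% to 30.0% above are illustrations for one omitted group only.

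The 6-week cut-off is secondary. The window of 11 to 14 days follows from the text, but any shortfall rests on assumed late-response shares. An undercount of that kind would lead a later trial to send too many invitations, which is a correctable error.

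It would also be wrong to conclude that age standardisation solves the problem. It can adjust the age mix but cannot recover the previously invited groups at any age. The randomised comparison, the primary outcome and the sample size are not affected.

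**What to change.** 1. Replace the general-population wording with a statement that the participation and eligibility estimates apply to residents not previously invited to the programme, and list the frame among the limitations of those two outcomes.
2. Report participation as respondents divided by all people invited, and eligibility as eligible divided by respondents, at close of recruitment, with the 6-week figures beside them.
3. Report both rates and the risk-level distribution by 5-year age band. The participation denominators need the ages of all invitees, which would have to come from the programme's mailing records.
4. If an age-standardised figure is added, label it as not correcting for the omitted previously invited groups.

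The cost is a narrower claim and imprecise estimates in the sparse older bands. No new participant contact is needed, and all of it can be done at the reporting stage.

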### Conclusions

We are evaluating the effect of communicating individualized CRC risk information and screening recommendations on the choice of screening test in an organized screening program that currently performs the FIT and colonoscopy in a ratio of approximately 50:50. We hypothesize that we can increase FIT use among individuals at low risk and increase colonoscopy use among individuals at high risk, improving the risk-benefit balance of CRC screening. These results will be valuable to screening programs around the world with either a high use of colonoscopy, such as in the canton of Vaud, or FIT programs that may fail to recognize individuals at high risk who could derive additional benefit from colonoscopy over the FIT.

## Appendix

Multimedia Appendix 1 CONSORT-EHEALTH (Consolidated Standards of Reporting Trials of Electronic and Mobile Health Applications and Online Telehealth) checklist.

Multimedia Appendix 2 Questionnaires (English version).

Multimedia Appendix 3 Questionnaires (French version).

Multimedia Appendix 4 Intervention and control brochures (English version).

Multimedia Appendix 5 Intervention and control brochures (French version).

## Abbreviations

CONSORT: Consolidated Standards of Reporting Trials
CONSORT-EHEALTH: Consolidated Standards of Reporting Trials of Electronic and Mobile Health Applications and Online Telehealth
CRC: colorectal cancer
FIT: fecal immunochemical test
REDCap: Research Electronic Data Capture
SPIRIT: Standard Protocol Items: Recommendations for Interventional Trials
